## 1.0 Abstract

In Malawi, and other resourced-constrained sub-Saharan Africa (SSA) countries with high HIV burden, several service delivery models have emerged to increase PMTCT care retention for HIV-positive mothers and their infants by strengthening connections between health facilities and their surrounding communities. Through this study, we will rigorously characterize three such models of “community-facility linkage (CFL)”, and compare their impact against each other and the standard of care according to routinely collected health outcomes for mother-infant pairs (MIPs), including maternal retention in care and viral suppression, and infant HIV-free survival. Specific objectives are to: (1) establish a clear typology for CFL models by describing the main components of, and key stakeholder perspectives on, three such models in Malawi; (2) Describe MIP health outcomes in each model, and compare outcomes across models and versus the standard of care (SOC); and (2a) Examine associations between individual components of CFL models and MIP health outcomes, controlling for confounding. We will complete our specific objectives by conducting an efficient two-stage cohort study. In the first stage, we will ascertain individual-level outcomes for a retrospective cohort comprised of *all* mothers enrolled in the national PMTCT program from July 2016 through June 2017 across approximately 40 health facilities and their surrounding communities in 5 districts representative of Malawi (each health facility and the surrounding communities to which the facility is responsible denotes one “facility catchment area” or “study site”). In the second stage, we will employ an epidemiological sampling method to prospectively ascertain MIP vital status, maternal viral load, and infant HIV status. Applying this method, we will create a nested cohort of approximately 1,200 randomly selected MIPs from our full retrospective cohort, including those lost to follow-up who will be traced in the community. For these MIPs, we will ensure viral load testing for ART-treated mothers and infants/ young children, and DNA PCR or HIV rapid testing for infants/ young children, and revise outcomes estimates for the full cohort accordingly. Such a two-stage approach will enable us to efficiently make robust inferences about the comparative impact of different CFL service delivery models and their main components under routine programmatic conditions. Study findings will identify components of community-based MIP support that are associated with maternal care retention and infant HIV-free survival to refine and accelerate scale up of promising CFL practices in Malawi and SSA. It is envisioned that this study will also increase local capacity to conduct high-impact, HIV-related operational research to build upon our findings, and further accelerate Malawi’s progress toward achieving national 90-90-90 targets.

## 2.0 Background and Justification

Despite the impressive maternal and child health gains generated by the Option B+ and test and start strategies in Malawi, including increased maternal ART access and decreased rates of vertical transmission, client attrition from the PMTCT care continuum threatens recent progress. As many as 15% of HIV-positive pregnant women do not start ART, and another 31% become lost to follow-up within 12 months of treatment initiation. Similarly, high loss to follow-up is seen among HIV-exposed infants under 12 months of age and young children 12 months of age and older (henceforth referred to as “HEIs”), with 21% and 36% out of care by 12 and 24 months of age, respectively. Such mother-infant pair (MIP) drop-out from the PMTCT continuum has deleterious “downstream” effects, as failure to deliver quality PMTCT services—including HIV diagnosis, treatment, and care for mothers and infants—leads to higher vertical transmission rates and worse clinical outcomes for HIV-positive mothers and HEIs alike. Taken together, the effects of client loss from the PMTCT continuum may undermine Malawi’s progress toward ambitious UNAIDS-endorsed 90-90-90 targets.

To improve MIP care retention in Malawi, several models have emerged to strengthen community-facility linkage (CFL), a concept defined as any “formalized connection between a health facility and the communities it serves to support improved health outcomes”. Similar to other SSA settings, three models have been widely implemented to complement Malawi’s National PMTCT Programme and enhance the standard of care (SOC). Under the current SOC, Ministry of Health (MOH) Health Surveillance Assistants (HSAs), a cadre that moves between clinics and decentralized “health posts” to enact a broad array of public health activities, support PMTCT clients primarily through health talks and tracing of MIPs who have defaulted from HIV care. However, HSA staffing levels are often insufficient to meet needs in the community (approximately 1 HSA per 1,000 households), and the resources and person-time available to HSAs to support dedicated PMTCT activities has historically been limited. In contrast, the three most common CFL models—1) mentor mothers; 2) expert clients; and 3) community health workers (CHWs)—mostly or exclusively have a PMTCT focus and offer intensive psychosocial support to PMTCT clients. Mentor and expert clients are types of peer health workers—women living with HIV who offer longitudinal health education and psychosocial support, often via peer group meetings, to PMTCT clients. CHWs are community-based health workers who provide clients with psychosocial support, promote medication and appointment attendance, accompany clients to health facilities for clinic visits, and support the services provided by other, often facility-based, health

workers. All three models mobilize their respective CFL “provider”—i.e. the mentor mother, expert clients, or CHW—to trace HIV-positive women and HEIs who fall out of care, and encourage these women and infants to return to the clinic by phone contact or by targeted home visits in the community.

While the rationale underpinning these models has been supported by evidence generated from general ART and PMTCT programs across SSA, a rigorous description of each model, including their unique and shared characteristics, and the extent to which the models are implemented with fidelity to their design, is currently unavailable. Moreover, a clear understanding of each model’s major activities and defining features, including levels of CFL provider remuneration, supervisory structures, provider-to-client ratios, and relationships with clients and the formal health system, is similarly lacking. Finally, how and to what extent these components, both individually and collectively as part of CFL models, impact MIP care retention and joint health outcomes has not been well characterized, particularly in the era of test and start and against UNAIDS established 90-90-90 benchmarks.

### 3.0 Literature Review

Employing a public health approach to PMTCT, the Option B+ strategy of universal test and treat for pregnant and breastfeeding women has saved countless maternal lives and averted thousands of paediatric HIV infections in Malawi and elsewhere in SSA. In just its first year of implementation in Malawi, Option B+ increased maternal ART uptake by over 700%. However, despite these laudable achievements, sustaining mothers on ART and ensuring that they and their infants receive the full benefits of retention along the PMTCT care continuum remains a major challenge.

Interrupting the PMTCT care continuum at multiple points are a variety of psychosocial, health system, and structural barriers. These barriers encompass lack of social support, fragmented social networks, gender inequality, infrequent male partner involvement, internalized and enacted HIV stigma, high travel and opportunity costs for accessing facility-based HIV services, and limited counselling to facilitate acceptance of a new HIV diagnosis, among other barriers.

To mitigate these barriers, new and evolving strategies have been proposed that deploy lay health workers and peer cadres from the community to engage MIPs and bridge service offerings between communities and facilities. For PMTCT programs, these lay cadres have traditionally included community health workers (CHWs), mentor mothers, and expert clients, each of whom engage MIPs at community and/or facility levels to provide psychosocial support along the PMTCT care continuum. While data regarding the impact of these cadres are still emerging, programs involving lay health workers have demonstrated early promise for improving maternal HIV prevention knowledge and uptake of such PMTCT services as HIV testing & counselling (HTC), ART, and early infant HIV diagnosis (EID).

CHWs are a trained cadre of lay health worker that promote public health, link clinics and communities through referrals and home visits, and enhance uptake and delivery of health services. CHWs may facilitate or directly provide a host of health services in response to the clinical and public health issues faced by their communities, ranging from counselling on maternal health and breast-feeding, supporting persons with mental illness, managing malaria and other uncomplicated paediatric diseases, and providing health education for chronic conditions such as HIV/AIDS, tuberculosis, and non-communicable diseases, among others. How CHWs are organized can vary widely based on their employer (i.e. government versus civil society), training and supervision, and compensation and opportunities for career progression. In SSA, CHWs have been deployed in numerous HIV care and ART programmes in a variety of country contexts. In Zambia, peer CHWs have been trained to provide home-based support and counselling for ART adherence, resulting in greater task shifting of health care worker responsibilities and decreased loss to follow-up in the national HIV programme. In Rwanda, a community-based HIV treatment programme providing comprehensive psychosocial support to PLHIV on ART, including longitudinal accompaniment offered by CHWs, resulted in 92% programme retention at 24 months post-ART initiation.

In Malawi, lay CHWs have been involved in a number of community-based care and treatment programs, including for palliative care, HIV-associated malignancies, and ART/ PMTCT, among others. For PMTCT, the *Tingathe* program provides a modest work-related stipend to CHWs who support HIV-infected pregnant women and their children from the time of their first ANC visit through

breastfeeding cessation or successful ART initiation for infants diagnosed with HIV infection. Using this approach, the *Tingathe* program has catalysed improvements in ART uptake (and uptake of other ARV prophylactic regimens prior to Option B+ introduction), facility-based delivery, infant PMTCT prophylaxis, and EID testing. Similarly, Partners In Health—Malawi/ Abwenzi Pa Za Umoyo (APZU), established a CHW program in 2006 to support primary care service delivery in rural Neno District. The APZU program employs over 700 trained CHWs district-wide who serve as health educators, accompany patients with HIV, TB and other maladies to health facilities, and strengthen linkages for patients to the formal health system, including for PMTCT services.

Mentor mothers are mothers living with HIV who are employed, trained, and supervised to support health workers in under-resourced health facilities to deliver services as part of the health care team. The impact of mentor mothers has been reported previously from PMTCT programs throughout SSA. In Zimbabwe, a MSF-managed program demonstrated that clients receiving mentor mother support were twice as likely to return with their infants for EID testing compared to unsupported clients. Clients interviewed in this program reported decreased stigma, greater empowerment, and increased agency to disclose their HIV status to their male partner(s) and successfully negotiate condom use. In Uganda, the mentor mother model improved 12-month ART retention for HIV-positive mothers at mothers2mothers-supported facilities compared to clinics without mothers2mothers (m2m) services (90.9% vs. 63.6%, respectively). Assessment of MTCT at the end of breastfeeding demonstrated a durable impact to the m2m model, with the rate of HIV acquisition among 18-month-old infants being 6.8% in m2m-supported facilities compared to 8.7% in facilities without m2m. In South Africa, the presence of mentor mothers yielded favourable results on process indicators for HIV status disclosure, clinic attendance, and safe breastfeeding practices. In Malawi, m2m manages mentor mothers in over 100 clinics nationally who lead group and individual counselling sessions to provide psychosocial support and health education to new mothers and pregnant women living with HIV.

Expert clients are an emerging cadre who, like mentor mothers, are women living with HIV and who have experience navigating the PMTCT care continuum. However, expert clients typically have functioned on a volunteer basis with a strong community focus to meet a broad service delivery mandate, undertaking tasks ranging from providing psychosocial support and leading community-

based support groups, offering facility-based counselling and vital sign measurement, and tracing HIV-infected women who disengage from care in their communities.

PMTCT programs involving CHWs, mentor mothers, and expert clients each take different approaches to engage MIPs, link facilities and communities, and reach populations of women who may not otherwise seek PMTCT services. Yet despite their promise, limited evidence rigorously describes these models, and the impact they and their components have on important joint PMTCT outcomes for mothers and their infants. Indeed, the impact of these CFL models, and the influence of the cadres who staff them, likely depends on a range of previously under-described variables, including levels of remuneration, frequency of client contacts, staffing ratios, supervisory structures and training, and relationships with clients and the formal health system. To bridge these knowledge gaps, identify the essential elements of CFL models, and, ultimately, improve combined outcomes for HIV-infected pregnant women and their infants in an integrated PMTCT continuum, rigorous impact evaluation and characterization of CFL models is urgently needed.

#### 4.0 Central Hypothesis

Our central hypothesis is that all three CFL models will be associated with increased MIP care retention, maternal viral suppression, and infant 12-month HIV-free survival compared to the standard of care, and that a CFL model featuring CHWs will be shown to be most effective, being associated with a higher proportion of HIV-positive women virologically suppressed and retained in care at 12 months, and infants alive, HIV-free and retained in care at age 12 months compared to other models. We further hypothesize that the following components of CFL models will be significantly associated with MIP retention in care and will constitute the most essential features of effective CFL models: low ratio of clients to CFL provider, high frequency of CFL provider-client interaction (i.e.  $\geq 1$  time per month), early “defaulter tracing” activities, and availability of one-on-one support from CFL providers.

## 5.0 Goal and Objectives

### 5.1 Overall Research Goal

To characterize widely adopted community-facility linkage models and rigorously assess the impact of the model and their components on MIP care retention and other priority maternal-infant health outcomes in Malawi.

### 5.2 Objectives

Our research objectives are:

1. To establish a clear typology for CFL models by describing the main components of, and key stakeholder experiences of and perspectives on, 3 common approaches in Malawi.
2. To describe MIP health outcomes in 3 CFL models, and compare outcomes across models and versus the standard of care using an epidemiologic sampling strategy.
  - 2a. To examine associations between individual components of CFL models and MIP health outcomes, controlling for confounding.

## 6.0 Methodology

### 6.1 Study Design Overview

We propose to rigorously define and compare three widely adopted models for community-facility linkage with each other and the standard of care using a mixed methods approach involving both quantitative and qualitative data collection.

For the quantitative component, we will first use stratified random sampling to select facility catchment areas in 5 Malawi districts where implementing partners have focused PMTCT programming. We will then visit each selected area to construct a retrospective cohort of HIV-infected women who entered the national PMTCT program and received CFL services or the SOC between July 1, 2016 and June 30, 2017. These dates have been chosen to align with the latest change to Malawi HIV guidelines supporting universal “test and treat” strategy, which became national policy on April 1, 2016 and reached stable rolled out on July 1, 2016. Using existing data, we will gather individual-level retrospective data on each woman and her infant from PMTCT enrolment through the child’s second birthday. Next, we will enrich these data using an epidemiological sampling method designed to overcome the limitations traditionally associated with retrospective data (e.g. missing data, outcome misclassification, etc.). In this second stage, we will randomly select a sample of women from our full

cohort to create our nested cohort. These women will complete a questionnaire about their experiences with CFL models and services, undergo viral load testing, and have their children ages 12–24 months receive HIV testing. Such prospective data collection will enable us to confirm primary outcomes, fill in missing data, and improve study data quality more generally.

For the qualitative component, we will conduct both rapid and in-depth site assessments. Rapid site assessments will encompass: 1) a structured CFL model survey; and 2) structured observations of clinic visits and of client interactions with expert clients, mentor mothers, CHWs, HSAs, and other MOH healthcare workers (HCWs) in the three models plus the SOC. In-depth site assessments will require CFL model surveys and structured observations as done with rapid assessments, but will additionally incorporate 3) focus group discussions (FGDs) with CFL providers and MOH HCWs; and 4) in-depth interviews (IDIs) with purposively selected key stakeholders, including members of District Health Management Teams (DHMT) and supervisors/ managers of CFL programmes. A final qualitative data collection activity will be IDIs with HIV-positive mothers from our nested cohort.

Data from the qualitative component will be used to achieve objective 1; data from the quantitative component will be used to realize objective 2; and data from both the qualitative and quantitative components will be used to complete objective 2a.

## 6.2 Study Setting

The study setting includes 5 districts representative of Malawi, with a diversity of partner- and government-supported PMTCT programming. The 5 districts, encompassing Salima, Lilongwe, Neno Zomba, and Mzimba North/South (considered as one district for the purposes of this study given their longstanding history as a single district until very recently), were purposively selected to reflect the breadth of Malawi’s demography—Neno, Salima, and Mzimba North/South are largely rural; Zomba is predominantly rural with a large peri-urban area situated in central Zomba town; and Lilongwe has a large, central urban pocket surrounded by peri-urban and rural locales.

## 6.3 Study Population

We will begin our study by reviewing existing data from a generalizable sample of women (and their infants/ young children) from selected facilities in the 5 districts meeting the following eligibility criteria:

- Newly diagnosed or having documented evidence of HIV infection between July 1, 2016 and June 30, 2017 in selected health facilities;
- Documented referral to or enrolment in Malawi's PMTCT/ ART program;
- Pregnant (at any gestational age) or breastfeeding at the time of HIV diagnosis/ positive HIV status identification;
- $\geq 16$  years of age at the time of PMTCT referral/ enrolment (includes adults and emancipated minors according to Malawi law);
- Received Antenatal or PMTCT services at a facility catchment area served by a CFL model of interest or SOC.

Existing, routine data for these women and their infants will form the basis for our full retrospective cohort. From these data, we will randomly select women and their infants (i.e. mother-infant pairs) to participate in the nested cohort.

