## **6.5.2 Study Procedures for Objectives 2 & 2a**

### **6.5.2.1 Objectives 2 & 2a Overview**

In “real-world” PMTCT programmatic settings where the absolute numbers of MIPs is large, prospectively ascertaining clinical outcomes, including maternal viral load and infant/young child HIV status, is often challenging for an implementation research study such as this one. Therefore, we will learn about MIP health outcomes using an efficient, two-stage cohort design.

In the first stage, we will retrospectively construct a cohort of HIV-infected women entering the national PMTCT program and receiving community-facility linkage (CFL) services or the SOC between July 1, 2016 and June 30, 2017 in our 40 randomly selected facility catchment areas. For all areas, we will review existing, routine MOH data for all eligible women and their infants to abstract retrospective data on our outcomes of interest—12-month maternal retention in care, viral suppression for HIV-positive mothers, and 12-month infant HIV-free survival. (Of note, maternal and infant outcomes have two different “starting points” for determining the 12-month outcome, which we will account for in our analysis—in the case of HIV-positive mothers the “starting point” is ART initiation date and for infants it is date of birth).

In the second stage, we will use epidemiological sampling to obtain outcomes on a nested cohort of approximately 1,200 randomly selected MIPs drawn from the full retrospective cohort (*see section 6.4 Sample Size*). Information will be collected from these 1,200 participating MIPs through a detailed questionnaire and blood sampling for maternal viral load and infant HIV testing, and will be enriched by qualitative in-depth interview (IDI) data for 60 women purposively selected from among the MIPs in the nested cohort. IDIs will explore maternal perceptions, experiences, and satisfaction with CFL models and services, including with their key components, and how these services have affected their longitudinal engagement with and retention in the national ART program.

Data from the first and second stages will be combined to present the HIV care cascade for MIPs in aggregate, and by CFL model/ SOC, from HIV testing through ART initiation and viral suppression. Uptake of HIV services at the three main steps of the HIV care cascade will be calculated according to UNAIDS definitions and compared against established “90-90-90” benchmarks (*see section 7.2.2.2 below*).

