#### **Primary Outcome:**

- 12-month post-ART initiation retention in care for HIV-positive mothers

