#### **Secondary Outcomes:**

- Proportion of pregnant women newly registered in ANC who received HIV testing services
- Proportion of HIV-infected PMTCT clients initiated on anti-retroviral therapy
- 6-month post-ART initiation retention in care for HIV-positive mothers
- Proportion of HIV-positive mothers achieving HIV virological suppression from 6 months post-ART initiation (at MOH-recommended times of 6 and 24 months post-ART and, through the study, at time points between 12 and 24 months post-ART initiation)
- 12-month infant HIV-free survival
- Exposed infant “early” HIV infection status (i.e. HIV-1/2 DNA PCR result) from age 6 weeks
- 24-month child HIV-free survival
- 12- and 24-month infant HIV sero-status
- Median time from PMTCT enrolment to maternal ART initiation
- Median age of ART initiation for HIV-infected infants and young children
- Proportion of HIV-infected infants and young children achieving HIV virological suppression (from 6 months post-ART initiation per MOH guidelines)

- Proportion of HIV-infected mothers and infants who “returned to care” within 30 and 60 days of meeting the national ART program definition of loss to follow-up/ “defaulting” (i.e. not known to have transferred out, stopped or died AND have not returned to the clinic for 2 months after the woman is expected to have run out of ARVs).
- Proportion of HEIs who “returned to care” within 30 and 60 days of meeting the national HIV Care Clinic (HCC) programme definition of loss to follow-up/ “defaulting” (i.e. not known to have transferred out, stopped or died AND have not returned to the clinic for 2 months after the “next appointment date” given at the last HCC visit).

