## **7.2.2 Analysis Plan for Objective 2 & 2a**

### **7.2.2.1 Cohort Data**

We will calculate maternal retention in care as the proportion of mothers alive and in care at 6, 12, and 24 months post-ART initiation among all eligible women at the start of the cohort. We will also calculate median days from PMTCT enrolment to ART start to examine the effects of CFL models on time to ART initiation. We will look for differences in the delay of ART initiation across the CFL models and SOC using the Aalen-Johansen estimator to account for the competing event of death. We will report crude HEI mortality at 12 and 24 months as part of our survival analysis. We will define infant 12-month HIV free survival as the proportion of HEIs alive with a negative 12-month HIV-rapid test among all infants enrolled in the HEI birth cohort. Similarly, we will define infant 24-month HIV free survival as the proportion of HEIs alive with a negative 24-month HIV-rapid test among all infants enrolled in the HEI birth cohort. We will use Kaplan Meier techniques to compare infant HIV-free survival at 12 and 24 months across the 3 CFL models and SOC accounting for informative censoring and differences in baseline patient characteristics between the models using inverse probability weights. We will censor all survival outcomes on the last date of field activities in a given district (most likely between February 1, 2018 and April 30, 2019, depending on the district), the date of transfer, or the date of the last clinical encounter, as appropriate.

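### Eligibility sets no limit on ART start date, but primary retention is timed from ART initiation, so some women can enter the cohort after their 12-month outcome date

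*Protocol*

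**What the plan says.** Three parts of the protocol together define who is counted and from when.

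- **Who enters.** Section 6.3 takes women "Newly diagnosed or having documented evidence of HIV infection between July 1, 2016 and June 30, 2017 in selected health facilities". It requires "Documented referral to or enrolment in Malawi's PMTCT/ ART program" and that the woman be "Pregnant (at any gestational age) or breastfeeding at the time of HIV diagnosis/ positive HIV status identification". No criterion asks for ART-naive status or bounds the ART start date. Under section 6.1, entry to the national PMTCT programme falls between July 2016 and June 2017, and abstraction begins at PMTCT enrolment.
- **When the clock starts.** Section 6.5.2.1 says the maternal starting point "is ART initiation date and for infants it is date of birth". Section 7.1 gives the primary outcome as "12-month post-ART initiation retention in care for HIV-positive mothers".
- **Who is in the denominator.** For retention, section 7.2.2.1 counts "mothers alive and in care at 6, 12, and 24 months post-ART initiation among all eligible women at the start of the cohort".

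Section 7.1 also lists "Median time from PMTCT enrolment to maternal ART initiation" as a secondary outcome. The protocol does not say how a woman whose ART began before PMTCT enrolment is handled in either outcome.

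**The concern.** Take a woman who began ART in 2013, became pregnant, and had her known positive status recorded at antenatal care in September 2016. She meets the section 6.3 criteria on HIV status, programme enrolment and pregnancy. Her 12-month date fell in 2014. She had to survive past that date to be enrolled, and whatever she received from a CFL model or SOC in 2016-17 cannot have affected it. Her result still enters the primary comparison.

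A woman who began ART, say, 8 months before entry has her 12-month date after entry and can still be lost. She could not have died in those first 8 months and still entered, so that part of her follow-up is immortal time.

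Two consequences follow. Women whose outcome predates exposure add the same quantity to both groups and pull the difference towards zero. If they are more common under one model or in one district, they also create a difference that is not a model effect. In addition, their time from PMTCT enrolment to ART start is negative.

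**Working it through.** **Inputs.** From section 6.4: SOC retention 73%, difference 8 points (so 81% in CFL sites), two-sided alpha 0.05, n = 298 SOC and 894 CFL. Assumed, because the protocol gives no figure: q, the share of women whose 12-month date precedes entry (10% to 60%), and r, their retention at that date (90% to 100%). r is set equal in both groups because the exposure under study comes later.

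**Reproducing the stated power.** Continuity-corrected normal approximation for two proportions, women treated as independent:

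Power = Φ{ [Δ − c − 1.96·√(p̄(1−p̄)(1/n₁+1/n₂))] / √(p₁(1−p₁)/n₁ + p₂(1−p₂)/n₂) }, with c = (1/n₁+1/n₂)/2.

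- p̄ = (298×0.73 + 894×0.81)/1,192 = 0.79
- c = 0.0022; pooled standard error 0.0272; unpooled standard error 0.0289
- (0.08 − 0.0022 − 1.96×0.0272)/0.0289 = 0.84, and Φ(0.84) = 0.80

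This matches the stated 80%.

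**Dilution.** p_SOC = (1−q)×0.73 + q×r and p_CFL = (1−q)×0.81 + q×r. The difference is (1−q)×8 points whatever r is.

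| q | Difference (points) | SOC v CFL at r = 100% | Power, r = 100% | Power, r = 95% | Power, r = 90% |
|---|---|---|---|---|---|
| 0 | 8.0 | 73.0% v 81.0% | 0.80 | 0.80 | 0.80 |
| 10% | 7.2 | 75.7% v 82.9% | 0.75 | 0.74 | 0.73 |
| 20% | 6.4 | 78.4% v 84.8% | 0.68 | 0.67 | 0.65 |
| 40% | 4.8 | 83.8% v 88.6% | 0.54 | 0.49 | 0.45 |
| 60% | 3.2 | 89.2% v 92.4% | 0.37 | 0.30 | 0.25 |

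The loss does not depend on r being 100%. Lower r makes power slightly worse.

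**Differential share.** Suppose there is no true effect (73% in both groups among the other women), with q = 30% in SOC and 50% in CFL:

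- r = 100%: 0.7×0.73 + 0.3 = 81.1% v 0.5×0.73 + 0.5 = 86.5%, a spurious 5.4 points
- r = 90%: 0.7×0.73 + 0.3×0.9 = 78.1% v 0.5×0.73 + 0.5×0.9 = 81.5%, a spurious 3.4 points

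These shares are illustrative. The covariates named in section 7.2.2.1 are age, pregnancy number, district, facility type and cohort size, in an open-ended list; prior ART is not named.

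**What restriction does to power.** If the same 1,192 women are enrolled and a share q is set aside, n becomes 298(1−q) and 894(1−q) with 73% v 81% intact. Power is 0.76, 0.71, 0.58 and 0.41 at q = 10%, 20%, 40% and 60%. Restriction recovers the 8-point contrast; it does not recover 80% power.

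**The case against.** The strongest reply is that the authors meant new initiators. Section 6.4.1 sizes sites on newly diagnosed women and describes mothers newly enrolled into PMTCT. Section 7.2.2.1 analyses delay from enrolment to ART start and plans a subgroup of women who initiated ART while breastfeeding. Section 7.1 places study viral loads between 12 and 24 months after initiation, which cannot fit a 2013 starter. This stands as evidence of intent, and a reader should not infer a deliberate decision to include established ART users. It does not close the gap. Being newly enrolled in PMTCT is not the same as being newly on ART, site volume selects sites rather than women, and the second limb of "Newly diagnosed or having documented evidence of HIV infection between July 1, 2016 and June 30, 2017 in selected health facilities" has little function unless women with known infection qualify. Section 7.2.2.2, for a different indicator, accepts known receipt of ART as evidence of positive status.

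Two stronger readings are tempting and not supported:

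- **That every woman on ART before this pregnancy has an outcome date before entry.** This is true only if ART began at least 12 months before entry.
- **That such women are retained by construction.** Entry guarantees survival to the earlier date, not being in care on it. A woman could have been out of care at month 12 and returned in this pregnancy, and section 6.3 accepts documented referral without active care. Being in care is likely, not certain.

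It is also fair that a statistical analysis plan could narrow the analysis set. But eligibility, time zero and denominator are all stated in the protocol, and followed as written they give the result described.

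**Conclusion.** The point holds. Section 6.3, the ART-initiation clock in sections 6.5.2.1 and 7.1, and the all-eligible denominator in section 7.2.2.1 do not fit together, and the primary outcome is affected. As written, the plan counts women whose outcome was settled before exposure in the study window, plus others with partial immortal time.

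The size cannot be fixed from the document. Over assumed shares of 10% to 60% and retention of 90% to 100% in both groups, the difference falls from 8 points to between 7.2 and 3.2, and power from 0.80 to between about 0.75 and 0.25. These figures concern only women whose 12-month date precedes entry; applying them to everyone already on ART would overstate the loss. Dilution follows whenever such women are included and a true difference exists. Bias from an unequal share is a possibility: nothing in the protocol shows that the share differs by model.

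**What to change.** Reconcile sections 6.3, 6.5.2.1 and 7.2.2.1:

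1. Restrict the primary retention analysis and the time-to-ART outcome to women whose ART start date is on or after PMTCT enrolment or positive-status identification in July 2016 to June 2017, with the clock at ART start.
2. Report women already on ART at entry as a separate stratum, with the 6-, 12- and 24-month clock at PMTCT enrolment. This also deals with those who started less than 12 months earlier.
3. Restate the power given for 1,192 mothers for the restricted population, once the share already on ART is known from the enumerated cohort.

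This can be done at the analysis stage. Section 6.6.3 already abstracts ART start and programme enrolment dates, and section 6.5.2.3.2 orders the enumeration list by date of PMTCT referral or enrolment. It should not require a split nested-cohort draw, which could strain site targets. In Table 3, stratum 8 has 60 to 100 mothers available for 60 sampled, and stratum 16 has 50 to 100 for 90. If those counts include women already on ART at, say, 40%, only 36 to 60 and 30 to 60 new starters remain.

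The cost is fewer women in the primary analysis. Keeping 1,192 new starters would need 1,192/(1−q) enrolled, for example 1,490 at q = 20%; otherwise the lower power should be stated.
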